### Knee OA symptoms and health quality of life

**Brief Pain Inventory (BPI)** – short version. A consensus panel, the Initiative on Methods, Measurement, and Pain Assessment in Clinical Trials (IMMPACT) recommended the inclusion of the short version of Brief Pain Inventory (BPI) in all trials that intend to assess chronic pain [81]. It is a widely used, reliable, valid instrument that assesses pain history, location, intensity and its interference with daily activities in individuals with osteoarthritis [82]. The Portuguese version was validated and recent studies have provided strong support for its reliability and validity [83,84].

**Numerical Rating Scale (NRS).** The subjects shall learn to self-assess their knee intensity pain via the 0–10 point NRS. The NRS should be used to control pain intensity before and after the aquatic exercise class and whenever is necessary.

**Knee Injury and Osteoarthritis Outcome Score (KOOS).** This questionnaire includes 5 dimensions to measure KOA specific health-related quality of life (QOL), knee pain (Pain), other disease-specific symptoms (Other Symptoms), activities of daily living (ADL), sport/recreation function (Sport/Rec). A score in each of the five dimensions is calculated as the sum of the items included and then converted according to a 0–100 scale, with 0 representing extreme knee problems and 100 representing no knee problems. The KOOS is validated for patients with knee injury or with knee OA and is a reliable and responsive self-administered instrument for short-termfollow-up [85]. The Portuguese validation has acceptable reliability with Cronbach’s alpha coefficients between 0.77 and 0.95, and ICC ranging from 0.82 to 0.94 for the KOOS subscales [86].

Medical Outcomes Study **(MOS) Short-Form Health Survey (SF-12v2).** SF-12 v2 consists of a subset of 12 items to assess health status, organized into two domains: Physical (Physical Component Summary, PCS) and Psychological (Mental Component Summary, MCS) that make up the original SF-36 [87]. It has been shown that the SF-12 correlates highly with SF-36 in both obese and non-obese patients [88]. The Portuguese version of SF-12 has satisfactory reliability and validity [89,90].

**Beck Depression Inventory (BDI-II).** This instrument, developed by Beck and colleagues [91] has 21 items to rate the severity of depression according to the clinical definition. It is one of the most popular and widely used instruments for assessing the severity of depressive symptomatology. The Portuguese version [92] shows a good internal consistency, a factor structure very similar to the original version [91,93], and an adequate convergent validity.

### Physical function

**Six Minutes Walking Test (6MWT).** The distance (d) and gait speed (v) of the 6MWT is used to assess the aerobic capacity and the walking ability. It will be performed individually and according to the *American Thoracic Society protocol* (ATS) [94], in a controlled indoor environment 46 meters in length and rectangular in shape. The 6MWT is highly reproducible in obese individuals (r = 0.926; 95% CI 0.816-0.972, P < 0.001) [95], and it has been used in studies with KOA [75,96-100].

**Chair Sit and Reach test (CSR).** The CSR test is a safe and socially acceptable alternative to traditional floor sit-and-reach tests as a reasonably accurate and stable measure of hamstring flexibility [101]. The subjects shall be allowed three attempts for each limb and the best of these scores shall be recorded to the nearest centimeter.

**The Back Scratch Test (BS).** The BSS is a measure of overall shoulder range of motion which involves measuring the distance between (or overlap of) the middle fingers behind the back with a ruler [102]. After a familiarization trial, this test is assessed twice, alternately with both hands, and the best value of each registered.

**Five-Repetition Sit-To-Stand Test (FRSTST).** This is a widely used measure of functional strength. ICC values for it demonstrate from good to high test-retest reliability for adults and subjects with osteoarthritis [100,103,104].

### Strength

**Knee Strength.** A dynamometer Biodex System III (Biodex Medical Inc., Shirley, NY, U.S.A.) will be used for isokinetic assessment of knee strength (flexor and extensor muscles) and isometric knee strength, bilaterally. The first leg to be tested shall be the less affected leg or, in doubtful cases, the dominant leg. Gravity correction to torque is calculated at 45 degrees (0 = straight leg). The range of motion for testing is pre-determined from 20° to 80° for all subjects. The exclusion of extreme ranges of knee motion was established due to the fact that they are known to be painful and frequently non-executable by these patients, namely full extension due to quadriceps weakness Similar procedures, according to the dynamometer used, have been adopted in other surveys involving the same population [105-110].

Maximal Isokinetic Strength is measured on a concentric/concentric mode, at angular velocity of 60°/s. Among the low velocities’ group, the 60°/s have been used in other studies and should provide better stability for this population [111]. The subjects should perform one set with minimum overload for habituation and 2 sets of 3 repetitions with a 120-second rest between sets. The subjects should be oriented to perform the test by exerting maximum pressure on the isokinetic arm through the entire range of movement. During the test vigorous verbal encouragement shall be given to each subject. The set with higher extension peak torque together with the lowest coefficient of variation will be chosen for analysis.

The angle of best torque of the knee extension obtained from each subject in the isokinetic test should be chosen for the isometric test. Maximal knee extension isometric test will be applied in one set of 3 repetitions during 5 seconds with 30 seconds relaxation interval between repetitions. The best of the three force-time curve will be chosen according to the higher peak.

Prior to measurement, the subject shall be are seated on the dynamometer with knee and hip joints at 90°. Crossover shoulder, belly and knee straps, as well as a lap belt will be used to restrain the subjects movement. The lever arm pad is strapped around the lower leg, 2 centimeters above the lateral malleolus of the fibula. The axis of rotation of the dynamometer should be aligned with knee joint’s axis of rotation. Joint warm-up will be done by gentle free movements of flexion and extension of the knee.

**The Handgrip Strength Test (HST).** This test evaluates maximal isometric force of the muscles of the hand and forearm. Although the sample of this study will not have hand OA, this test has been used in obese individuals as an indicator of total body strength and functionality [112,113]. The adopted protocol for this project is the same that was used for Portuguese adults in the national observatory [114]. Prior to the test, the grip dynamometer should be adjusted to the size of the hand of each subject. Subject will be standing with arms along the body without contact with the trunk and elbow slightly bent at 200°. Testing is first done by dominant hand followed by the non-dominant one. The force must be performed during the expiratory phase and valsalva maneuver should be avoided. After three trials, if the difference between each value is within 3 kg, the test is considered completed. If a bigger difference is observed, then the test will be repeated after sufficient rest time. The best repetition will be chosen for further analysis.

### Morphology and body composition

**Body composition.** Body mass index will be calculated as mass (measured in kilograms by a standard calibrated scale) divided by height squared (measured in meters). A DXA scanner (QDR 4500A, fan-beam densitometer, software version 8.21; Hologic, Waltham, USA) will be used to measure whole body lean mass (LM), fat mass (FM) and bone mineral content (BMC). DXA measures the attenuation of X-rays pulsed between 70 and 140 kV synchronously with the line frequency for each pixel of the scanned image. According to the protocol described by the manufacturer, a step phantom with six fields of acrylic and aluminum of varying thickness and known absorptive properties shall be scanned alongside each subject to serve as an external standard for the analysis of different tissue components. The same technician shall position the subjects, perform the scans and execute the analysis using the standard analysis protocol. Based on test-retest using 10 subjects, the coefficient of variation (CV) in PICO staff for FM and FFM was 2.6 and 1.5% respectively, and the total error of measurement (TEM) and the CV were 0.02 kg and 1.7% respectively.

**Anthropometry.** The anthropometric measurements that shall be collected by this study shall include height, body mass, perimeters (waist, hip, middle thigh, patella shank and foot breadth. The aforesaid measures shall be collected by an ISAK accredited anthropometrist using procedures established by ISAK [115] except in the case of patellar circumference, foot diameter and abdominal sagittal diameter, which shall be obtained according to previously validated procedures [116-118]. The intra-observer technical error for circumferences and diameters measures in the pilot study ranged from 0.2 -0.4.

### Gait analysis

The gait protocol used on the present study was adapted from IDEA study [77], taking into account our laboratory specific equipment.

Data collection and analysis: Motion capture of the gait will be collected with 10 cameras Qualisys (Oqus-300) operating at a frame rate of 200Hz. Forty six reflective markers should be placed in predefined anatomical protuberances and used for the reconstruction of lower limb segments using Visual 3D software (C-Motion, Inc., Germantown, MD). To reduce noise, the motion data is filtered, using a low pass Butterworth filter, with a cutoff frequency of 15Hz [119]. Ground reaction force will be collected with two force platforms (Kistler AG, Winterthur, Switzerland) and AMTI (Advanced Mechanical Technology, Inc, Watertown, MA), synchronized with the motion capture system.

The test will be performed in a fifteen meters walkway, six successful trials are collected from each participant and three should be chosen for subsequent analysis. A trial consists of starting on the platform approximately 2 meters behind the initial timer and walking past the first beam of light to activate the timer. As the participant walks and passes the second beam of light the timer will stop and speed will be recorded. The participant will turn around and wait for orientations to perform similar trial in the opposite direction.

In general, KOA subjects walk at a slower speed and cadence, with a prolonged stance phase, presenting a static and dynamic varus alignment, showing smaller flexion and greater knee adduction moment (KAM) [12,34,120,121]. The following kinematic and kinetic outcomes should be analyzed from the gait test:

#### *Gait speed*

Freely chosen speed is slower in individuals with Knee OA being correlated with high ground reaction forces during heel strike [77];

#### *Gait cycle characteristics*

Swing and stance phase duration, stride frequency, stride length, knee and hip ROM and angular velocity;

#### *Ground reaction forces*

The vertical, anteroposterior and mediolateral force components will be recorded with a force platform. Computer software will be used to calculate duration, amplitude and impulse of the reaction forces;

#### *Knee adduction moment (KAM)*

Knee adduction moment (KAM) is considered a valid parameter to infer the level of mechanical loading [122]. Healthy subjects show substantially higher abduction moments than OA subjects and the external adductor moment has been linked to the development and progression of medial compartment OA in association with the varus alignment installation by increasing the compressive forces across the knee [123]. In addition, there is a significant inverse association between the peak of knee adduction moment during late stance and the amount of knee pain which may represent a compensatory mechanism to reduce medial tibiofemoral joint load in the setting of knee pain [124];

#### *Adduction angular impulse (AddImp)*

The integral of the frontal plane external joint moments (adduction and abduction) over time during the stance phase, providing a functional measure of gait rather than normalized KAM. This measure has been useful to distinguish loads in different OA severity [125,126];

#### *Knee extension moment*

Individuals with knee pain and weak muscles, as a protective mechanism, seem to avoid the quadriceps muscle recruitment during load acceptance in stance phase, showing a reduced knee peak extension moment;

#### Hip extensor moment

OA subjects walking at similar speeds of healthy one’s maintain their walking speed by increasing hip range of motion and its speed. Greater hip extensor moments may indeed help to maintain walking speed, but this does not appear to be the case with the hip flexor and ankle plantar flexor moments, which were substantially lower;

#### *Hip external abduction moment*

Individuals with knee OA seems to have a higher involvement of hip adductor muscles to compensate a weak quadriceps and hip abductors [12,127].

Since this is a longitudinal study, walking speed may change and should be measured at each testing moment (baseline and after intervention). One successful trial is defined as the one in which the participant’s entire foot is placed on the surface area of the force platform while walking within ± 3.5% of the freely chosen speed.

The freely chosen speed should be assessed in the biomechanical test day before the placement of markers, in so far as each subject shall walk barefoot in the walkway until a stabilization of walking speed is observed. Usually the latter stabilization occurs after crossing of the walkway 5–6 times. The speed is monitored using an infrared photocell control system (Model E3F2-R4B4-M, OMRON) set with 7.3 m apart at the hip level, interfaced with a processor specifically built to record the time and calculate the speed as a function of the distance.

### Lifestyle

#### *International physical activity questionnaire (IPAQ)*

The short form of IPAQ was chosen because it is easy to apply. Despite its liability having been verified in many countries and with different populations [128-130], studies have indicated that the IPAQ-SF typically overestimates physical activity [131]. However, this instrument will be used for controlling the amount of physical activity along the study, and not for any classification of physical activity level. All participants shall receive a previous explanation about how to complete the questionnaire, and their answers will be confirmed during the interview. Data will be processed according to IPAQ guidelines [132].

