#### *Study aim*

To design an aquatic exercise program specific to knee osteoarthritis, with the goal of management of OA symptoms and the improvement of physical fitness. The PICO program is based around the first step for weight loss interventions in individuals with KOA being the control of pain and other symptoms. When KOA symptoms are controlled, patients learn that it is possible to live with the disease which in turn motivates lifestyle changes. The increase of physical activity due to lifestyle changes may then cause improvement in body composition. In this way 6 hypotheses are formulated: H1. 3 months of aquatic exercise will improve KOA symptoms (pain and stiffness) and physical function in obese individuals with KOA; H2. The gait parameters (gait speed, gait cycle, ground reaction forces and knee forces moments) of obese individuals with KOA can be improved by aquatic exercise; H3. Beyond fitness component and the exercises skills, aquatic exercise group classes can work as an educational component and to promote lifestyle changes. H4: The aquatic exercise program can improve mental status and quality of life. H5: The aquatic exercise program can cause a weight reduction or body composition change. H6: 3 months of aquatic exercise can have a positive effect on selected inflammatory biomarkers of KOA.

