### Intervention programs

#### *Aquatic exercise (AE)*

The aquatic program is based on the guidelines of OARSI and EULAR for KOA management [28,29], on the Aquatic Exercise Association Guidelines (AEA) [72], on the Arthritis Foundation Aquatics Program instructor’s manual [73], on the ACSM’s Guidelines for Exercise Prescription [76] and on analysis of the protocols of previous studies [36,38,39,44,77,78].

The strategies in the PICO proposal to produce a high quality aquatic exercise intervention are structured according to AEA guidelines [72] and include overload assessment and managements, impact level control (level 1, 2 or 3), exercise cadence control and adequate music according to exercise goals. In addition the use of different and pre-defined cool-down sessions each week, a strong motivational component and pain assessment should make the difference in this protocol. Educational themes shall also be addressed during the classes. One educational theme per week shall be reinforced, such as: *What did you have for breakfast? Let’s try, during this week, to improve the quality of our breakfast. Next class I will check what you ate; remember that you should assess yourself about knee pain, let’s try to learn how to live with it.*

Another aspect that will be considered is the level of aquatic ability of each participant. Exercises like underwater breathing and flotation will be used in small doses to reduce fear of water and to ensure that participants are comfortable moving around the pool.

The aquatic program will be organized into 24 sessions distributed over 12 consecutive weeks, with a frequency of twice a week. The duration of each session will be 60 minutes, being that 10 minutes are for patient reception, blood pressure control, pain registry etc., and the effective time inside the water is 45 minutes. The indoor pool works with an air temperature around 27 ± 1°C and water temperature is controlled at 30.5 ± 0.5°C.

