**Life style**			
Physical activity level (IPAQ)		x	x

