**Inflammation biomarkers**			
Cytokines (blood drawn)		x	x

The main outcomes will be KOA symptoms (pain and stiffness) and quality of life, physical function (aerobic capacity, strength, and flexibility) and gait (kinetics and kinematics). The secondary outcomes are body composition, morphology, physical activity level, and inflammatory biomarkers. During the study, all participants will be allowed to maintain their usual medication, including analgesics and NSAIDs. A detailed record of medication will be done at baseline and 3 month post-intervention testing.

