With the exception of the knee radiographs for OA diagnosis, all measures will be obtained in the same facility at the baseline and immediately after the end of the program. One barrier at each visit/measuring point will be the capacity to asses all participants in a short interval. Due to the specificity of the outcomes will be necessary to manage the schedule among four different labs. Therefore, to support the project, staff team includes one secretary responsible for administrative work, four technicians conducting the dynamometer tests, gait analysis, body composition and anthropometry assessments and one professional for collecting blood samples. Each technician received the responsibility to be specialized in two test’s group plus questionnaires and, to avoid inter-rater error, the same technician should lead its application in both assessments, baseline and post-exercise intervention. Participant adherence to exercise is one of the main challenges, therefore to avoid drop outs, motivational cues, intra-group social interaction, frequent telephone calls and the quality of instructors are the main strategies chosen to contribute to adherence rates. Besides, since our sample will include adults that may still be working which will create some difficulties in the definition of class schedules, one extra class, every 15 days, will be provided to enhance high compliance, and to allow that all participants might attend to 24 sessions during the 3 month period over which the study shall run.

One possible constraint to the success of the aquatic exercise programs would be the level of water skills of each participant. Although it is not necessary to know how to swim, the autonomy and the ability to apply power against the water are essential to get benefits from this type of activity, especially when performing strengthening exercises. Therefore some aquatic adaptation exercises will be introduced in the class format (Table 1).

Our study is based on the premise that individuals with KOA need a wide exercise intervention, adapted not only to the affected joint but to the health status of the patient, working the whole body and the mind simultaneously. In addition, we expect that aquatic exercise, beyond the improvement of KOA symptoms, can increase the symmetry between forces in the lower-limb joints (adduction/abduction and flexion/extension moments at knee and hip joints), so improving gait.

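### The protocol article gives the IPAQ two roles, and its 3-month total can include up to 90 min/week of class time in the aquatic arm only, so it cannot be read as lifestyle change under H3

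*Protocol article*

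**What the plan says.** In the paragraph after Table 2, the protocol article states: "The secondary outcomes are body composition, morphology, physical activity level, and inflammatory biomarkers". The Life style block of that table assigns physical activity level to the IPAQ, at baseline and 3 months. The IPAQ section describes the purpose differently: "this instrument will be used for controlling the amount of physical activity along the study, and not for any classification of physical activity level". It adds that participants will be told how to complete the form and that "their answers will be confirmed during the interview". It does not say whether class time counts, and it gives no recall window.

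Under Study aim, H3 is that "aquatic exercise group classes can work as an educational component and to promote lifestyle changes". The same section expects lifestyle change to raise physical activity, and that rise to improve body composition.

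The aquatic program consists of "24 sessions distributed over 12 consecutive weeks, with a frequency of twice a week", with 45 minutes of each session spent in the water. Under Educational program, the control group has no exercise program and attends weekly educational sessions instead. On timing, the Discussion says that, radiographs apart, "all measures will be obtained in the same facility at the baseline and immediately after the end of the program".

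**The concern.** Two things need attention.

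First, a reader cannot tell whether the IPAQ is there to test an effect or to monitor activity during the study. The two uses call for different handling and different reporting.

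Second, the follow-up falls where the questionnaire may pick up the intervention itself. If the recalled period overlaps the last weeks of classes, the aquatic arm reports prescribed exercise that the control arm was never offered. A gap between arms could then arise with no change in what participants do outside the pool. It would look like support for H3 when it showed only that the classes were attended. The same minutes could also hide a real gain in everyday activity among controls, whose educational program aims at healthier habits.

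**Working it through.** **Role of the instrument.** Set side by side, Table 2 and the paragraph after it make physical activity level an outcome measured by the IPAQ. The IPAQ section calls it a control instrument and excludes classification. No other instrument settles the matter. The WALI sections to be used cover alcohol, tobacco, diet and clinical history. KOPS touches on activity level, but Table 2 schedules it at screening and 3 months, not at baseline.

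**Class time.** The article states no figure for this quantity, so there is none to reproduce. The inputs are 24 sessions, 12 weeks and 45 minutes in the water (Aquatic exercise section), and no exercise program for controls (Educational program section).

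- Sessions per week: 24 / 12 = 2, which agrees with the stated frequency.
- Aquatic arm: 2 x 45 = 90 min/week in the water (2 x 60 = 120 by full session length).
- Control arm: 0.
- Possible built-in difference: between 0 (no overlap) and 90 min/week (full overlap).
- For scale, entry requires no program of more than 30 min/week of formal exercise, and 90 / 30 = 3. That limit concerns exercise programs and is not an IPAQ total.

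**Whether the planned analysis removes it.** The Statistical analysis section compares mean change between groups by ANCOVA adjusted for the baseline value of the outcome. Class minutes arise only after baseline, so this adjustment leaves them in the difference.

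**How often it could reach significance.** Assume full overlap and no change in activity outside class. With n per arm and standard deviation SD of the analysed score, the normal approximation to the chance of two-sided p < 0.05 in favour of the aquatic arm is

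Φ( 90 / (SD x √(2/n)) − 1.96 ).

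For n = 20 and SD = 100: 90 / (100 x 0.316) = 2.85; 2.85 − 1.96 = 0.89; Φ(0.89) ≈ 0.81.

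The article gives no SD, so the values below are assumptions. It does not say whether its 20 completers and 25 entrants are per arm. I take 20 and 25 as per-arm illustrations.

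| Assumed SD (min/week) | 20 per arm | 25 per arm |
|---|---|---|
| 60 | 99.7% | about 100% |
| 100 | 81% | 89% |
| 150 | 48% | 56% |
| 200 | 30% | 36% |
| 300 | 16% | 18% |

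With no true or built-in difference, the chance in this direction would be 2.5%. If only half the class time were captured (45 min/week), the result at SD 100 would equal the SD 200 row (30% with 20 per arm), since 45/100 = 90/200.

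**Blinding.** Study design says that data collectors are blinded. The Discussion gives each technician two groups of tests plus questionnaires. The Knee Strength paragraph calls for strong verbal encouragement during dynamometry. IPAQ answers are checked at interview. The article does not say who interviews or in what order.

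**The case against.** Several stronger readings are tempting, and the article does not support them.

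- A reader might infer that the IPAQ section denies physical activity the status of an outcome. It does not. It rules out sorting people into activity levels, and a continuous change in amount remains compatible with the secondary outcome. The conflict is one of stated role and wording.
- A reader might take controlling to mean statistical adjustment, and conclude that part of the treatment effect would be adjusted away. The Statistical analysis section names no IPAQ covariate. Elsewhere the article uses control in the sense of monitoring, as for blood pressure and pain.
- A reader might conclude that the interview will unblind the technicians. It could, but neither the interviewer nor the sequence is given.
- A reader might say that H3 is bound to appear supported. H3 is not tied to the IPAQ alone, since diet and habits are covered by the WALI. The overlap is not known, and the chance of significance depends heavily on an assumed SD.

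Two further objections have force. Total activity, classes included, is a legitimate outcome: the Abstract expects the program itself to raise activity and metabolic rate. Class time could also be separated at the confirmation interview, and item-level scoring may sit in the full protocol.

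What remains is that the published text names the outcome, the instrument and the timing without distinguishing class time from other activity. If the classes are not identified when the questionnaire is given, later analysis cannot reliably separate them.

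**Conclusion.** The point holds in limited form. The IPAQ's role needs one consistent statement. A between-arm difference in total IPAQ at 3 months cannot be read as lifestyle change under H3, because up to 90 min/week of it may be prescribed class time in one arm only.

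The 90 minutes follow from the article's own schedule. How much of it enters the score depends on the recall window and the test date, which are not given. With full overlap, the chance of a significant result from class time alone runs from about 16% to over 99% with 20 per arm, across assumed SDs of 300 down to 60 min/week. Total IPAQ remains valid as a description of overall activity. Possible unblinding through the interview is a risk worth a precaution and is not established. The point concerns one secondary measure; only that precaution touches the main outcomes.

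**What to change.** 1. State the same role for the IPAQ in Table 2, in the list of secondary outcomes and in the IPAQ section.
2. At 3 months, record PICO class minutes as a separate item, or subtract attended class minutes using the attendance record. Use attended rather than scheduled minutes, because the Discussion provides an extra class every 15 days and attendance may differ from two per week.
3. Use IPAQ activity excluding class time as the physical activity measure for H3. Report total activity including classes alongside it as a separate quantity, so that neither is lost.
4. Hold the IPAQ confirmation interview after the strength, walking and gait tests, so that talk of recent activity cannot reveal allocation before they are done.

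With class time removed and activity outside class unchanged, the built-in difference falls from at most 90 min/week to 0, and the two-sided error rate returns to the nominal 5%. The cost is one extra item, one extra line of reporting and a set order of assessments.
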